### Adverse events

AEs include all detrimental or unintended indications, symptoms, or disorders derived from acupuncture therapy or the utilization of antidepressants, shall be managed following the agreed-upon protocol. The type and severity of all AEs should be diligently documented in the CRF. Needle pain, localized hemorrhage, palpitation, or dizziness both throughout and after the intervention are common AEs related to the EA treatment. Other prevalent AEs associated with drug treatment are migraines, nausea, abdominal bloating, and fatigue. If a severe adverse event (SAE) occurs, it should be reported to researchers and the Ethics Committee in detail within 24 hours of occurrence and assessed by the Treatment Emergent Symptom Scale (TESS) for further evaluation and management. Any subsequent recommendations issued by the Ethics Committee shall be conveyed to the Data Safety Monitoring Board (DSMB), which retains the authority to cease the trials at their discretion. The research team will actively monitor all recipients experiencing AEs until their resolution, particularly those participants who decide to withdraw owing to the occurrences.

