**Methods and analysis:**

This is a multi-site, single-blind, randomized controlled trial with two parallel arms. A total of 204 eligible patients will be randomly allocated to two groups: the EA group (receiving EA treatment with placebo drugs) and the ESC group (receiving escitalopram and sham acupuncture treatment). Treatment will last 12 weeks, with 3 sessions per week for the first 8 weeks, decreasing to 2 per week for the remaining 4 weeks. The primary outcome will be the score of the 17-item Hamilton Depression Rating Scale (HAMD-17), and the secondary outcomes will include depression recovery rate, depression remission rate, Patient Health Questionnaire-9 (PHQ-9), 36-Item Short Form Survey Instrument (SF-36), and the dose and frequency of ESC. The Treatment Emergent Symptom Scale (TESS) will be used to assess all adverse effects. Full details of the statistical analysis plan for the primary and secondary outcomes will be described in this article.

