### Design

This is a multi-center, patient-assessor-blinded, randomized, and controlled trial designed to evaluate the efficacy and safety of EA treatment in patients with mild to moderate first-episode depression and to compare the therapeutic effect between EA and ESC.

We will conduct this study at 4 centers, including Shanghai Municipal Hospital of Traditional Chinese Medicine, Shanghai Mental Health Center, Shanghai Pudong New District Nanhui Mental Health Center, and Shanghai Xuhui District Central Hospital. A total of 204 patients who meet the inclusion criteria will be recruited and randomly assigned into either group, receiving EA treatment with placebo drugs or ESC with sham acupuncture (SA) treatment. After a one-week baseline evaluation, participants will enter a nine-month observation period in this trial. Participants will receive the EA or SA treatment three times a week (every other day) for the first 8 weeks and twice a week (every two days) for the final 4 weeks. Participants will be assessed at the following time points: baseline (1 week before treatment), the 1st month of treatment (4 weeks after treatment starts), the 2nd month of treatment (8 weeks after treatment starts), the end of treatment (12 weeks after treatment starts), and follow-up (1 month, 3 months, and 6 months after treatment ends). All participants will complete the self-rated scales to assess their mental state and quality of life (see the detailed trial process in **Figures 1**, **2**). Throughout the trial, we will adhere to the Standards for Reporting Interventions in Clinical Trials of Acupuncture (STRICTA).

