### Outcome measurement

#### Primary outcome

The primary outcome will be the mean change in HAMD-17 score from baseline to week 12. The HAMD-17 is a questionnaire designed to evaluate the symptoms of individuals diagnosed with depression, which is an observer-rated questionnaire consisting of 17 items (15). The scale uses either a 3-point or 5-point rating system and has demonstrated strong reliability and validity, making it a widely used tool in both research and clinical settings. A higher overall score indicates a higher level of depression, with scores ranging from 0 to 54; scores of 0–6 indicate a normal person without depression; 7–16, likely or suspected to have depression; 17–24, mild to moderate depression; ≥25, severe depression. This outcome data will be collected at baseline, during the treatment phase (at 4, 8, and 12 weeks), and at the 16-, 24-, and 36-week follow-ups.

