#### Secondary outcome

The depression recovery rate is the percentage of patients with a HAMD-17 score ≤7 after 12 weeks of treatment. The recovery rate refers to the percentage of individuals who have successfully overcome or managed their symptoms of depression, and will be collected at 12 weeks.The depression remission rate is the percentage of patients between 8 ≤ HAMD-17 ≤ 12 after 12 weeks of treatment. The remission rate refers to the percentage of individuals who have achieved a significant reduction in symptoms of depression, which may involve some residual symptoms but not at levels that would meet the diagnostic criteria for depression. This outcome data will be collected at 12 weeks.The Patient Health Questionnaire-9 (PHQ-9) is an essential self-administered depression screening and diagnostic tool for screening and assessing patients’ depressive status (16–18). It consists of nine items that are easily and effectively used to understand a subject’s depression in the past two weeks. The total scores might be anywhere from 0 (no depression symptoms at all) to 27 (daily occurrence of all symptoms). The higher the total score indicates, the more severe the depression. This outcome data will be collected at baseline, during the treatment phase (at 4, 8, and 12 weeks) and at the 16-, 24-, and 36-week follow-ups.The 36-Item Short Form Health Survey (SF-36) is one of the most widely used quality-of-life assessment scales with good reliability and validity (19). It provides a comprehensive overview of the participants’ quality of life in eight dimensions: physiological functioning, physical functioning, somatic pain, general health status, energy, social functioning, emotional functioning, and mental health. Higher scores represent a better health status. This outcome data will be collected at baseline, and during the treatment phase (at 4, 8, and 12 weeks).The dose and frequency of drugs will be recorded by participants based on actual daily dosing from baseline to the 6-month follow-up period.

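### Adverse events are defined by attribution to treatment, which risks under-recording, and possibly unequal recording, of events judged unrelated

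*Protocol article*

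**What the plan says.** The Adverse events section opens with the definition: "AEs include all detrimental or unintended indications, symptoms, or disorders derived from acupuncture therapy or the utilization of antidepressants". It continues: "The type and severity of all AEs should be diligently documented in the CRF". The examples that follow fall into two lists, one tied to EA and one tied to the drug. Severe events have their own rule: "If a severe adverse event (SAE) occurs, it should be reported to researchers and the Ethics Committee in detail within 24 hours of occurrence". That sentence carries no causal condition of its own.

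Safety is part of the stated purpose. The Design section calls the trial "designed to evaluate the efficacy and safety of EA treatment in patients with mild to moderate first-episode depression", and the Conclusion expects the results to support EA as a low-risk option.

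Depression severity is measured separately from AEs. HAMD-17 is collected at baseline, at weeks 4, 8 and 12, and "at the 16-, 24-, and 36-week follow-ups". PHQ-9, a self-completed scale, follows the same schedule.

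**The concern.** A safety comparison usually starts from every untoward event, whatever its cause, and treats relatedness as a further item judged afterwards. Here the order is reversed: derivation from acupuncture or an antidepressant is part of what makes an event an AE. Someone has to form a view on cause before the event is recorded as one.

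Two things are at stake. The first is completeness: events thought unrelated can drop out of the AE record in both arms. The second is comparability: if attribution works differently in the two arms, the AE counts reflect that judgement as well as the treatments. A conclusion that EA is low-risk would rest on those counts.

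**Working it through.** The article gives no AE rates, attribution rates or safety hypothesis, so no arithmetic applies. The check is a reading of the relevant sections side by side.

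1. **Is the definition causal?** Yes. The phrase in "AEs include all detrimental or unintended indications, symptoms, or disorders derived from acupuncture therapy or the utilization of antidepressants" that ties events to acupuncture or antidepressants is a condition on cause. The examples, sorted by the treatment they belong to, support that reading.

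2. **Does another section override it?** No. The Abstract says "The Treatment Emergent Symptom Scale (TESS) will be used to assess all adverse effects", which is also the language of effects. The Statistical analysis section does not redefine AEs.

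3. **What does the CRF instruction then cover?** It covers all AEs, and so takes its scope from the definition. An event judged unrelated is not clearly within it.

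4. **Are severe events exempt?** This is unclear. The 24-hour rule states no causal condition, but a severe AE is a kind of AE and can be read as inheriting the definition. The route to the Ethics Committee, and from its recommendations to the DSMB, starts from these reports.

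5. **Which events are caught elsewhere?** HAMD-17 and PHQ-9 are scheduled in both arms at weeks 4, 8, 12, 16, 24 and 36, six post-baseline visits, whatever the cause of any change. The inclusion criteria refer to a suicide question in the Hamilton scale, so that item is rated at the same visits. Worsening mood and suicidality present at a visit are therefore measured.

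6. **Which events are not caught elsewhere?**
   - Intercurrent illness and other non-depressive events judged unrelated appear in neither scale.
   - The gaps between post-baseline visits are 4, 4, 4, 8 and 12 weeks (8−4, 12−8, 16−12, 24−16, 36−24). A deterioration that begins and resolves within a gap can be missed.
   - The primary outcome is a mean change, not a count of participants harmed.
   - Missing primary outcome data take the last observed value. A participant who deteriorates and leaves before the next visit keeps the earlier score in that analysis.

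7. **Could recording differ by arm?** It could, but this is not shown. Taken literally, nausea in an EA participant taking starch tablets cannot derive from an antidepressant, while the same symptom in an escitalopram participant can. In practice a blinded person may attribute it to the tablets in either arm. The article does not say who judges derivation.

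**The case against.** The strongest reply has four parts.

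- **The word is include, not only.** The sentence is loosely built and describes no formal causality check before CRF entry. This is fair: the text does not forbid recording unrelated events. It also does not require it, and no other sentence does.

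- **Worsening depression is already the main measurement.** A reader might infer that deterioration in the EA arm would never be counted. The documents do not support that: HAMD-17 and PHQ-9 record it at six visits in both arms. This stands for worsening present at visits. It does not cover unrelated non-depressive events or episodes between visits.

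- **Bias is not shown.** A reader might infer that the filter favours EA, because drug effects are familiar and readily attributed. Every participant receives real or sham needling and active or placebo tablets. Participants and assessors are described as blinded, and the acupuncturists, who know the allocation, are kept out of evaluation. This stands in full: a difference in recording is possible, but neither its size nor its direction follows from the text.

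- **An article condenses.** Relatedness fields, CRF instructions and AE tables may sit in the full protocol, so their absence here is no fault. The definition itself is printed, however, and can be reviewed as printed.

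A reader might also see a contradiction over TESS, since the Abstract uses it for all adverse effects while the Adverse events section has a severe event "assessed by the Treatment Emergent Symptom Scale (TESS) for further evaluation and management". There is none: using TESS for severe events does not exclude using it for the rest. The Abstract gives no visit schedule for TESS, and the figures that might show one are not available.

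**Conclusion.** The point holds in a limited form. The article makes attribution to treatment part of the AE definition, so untoward events judged unrelated need not be recorded as AEs. In a trial with safety as an aim, this risks under-recording and possibly differential recording.

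No size can be given. Any number of omitted events would need an assumed rate for which the article offers no basis, and equal omission in both arms would not by itself show bias. The conclusion assumes that site staff follow the printed definition and that no fuller document replaces it. It leaves the primary efficacy analysis untouched. It is worth correcting because the change is small and the planned safety claim depends on these counts.

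**What to change.** Reword the definition so that an AE is any untoward medical occurrence after randomisation (or after first treatment, with one starting point stated), regardless of cause. State that worsening depression and suicidality are included, even though they are also rated on the efficacy scales. Make relatedness to needling and to tablets a separate CRF field, judged by blinded study staff already in place. Report all-cause and related AEs by arm. State that the 24-hour rule for severe events applies whatever the cause.

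The cost is a change of wording, one CRF field and slightly more AE recording at existing visits. No visits or staff are added.

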### Statistical analysis

Analyses will be conducted on the intention-to-treat (ITT) population, which comprises all qualified participants who meet the inclusion criteria, have received the intervention at least once, and have provided at least one outcome assessment. In statistical analysis, any missing primary outcome data will be replaced by the last observed data point, in accordance with the ITT principle. Additionally, a Per-Protocol Set (PPS) analysis will be employed to assess those participants who completed the trial without significant protocol violations. Data analysis for this study will be performed using the statistical software SPSS V.24.0. Descriptive statistical analysis will be used for all demographic and clinical characteristics of subjects, such as sex, age, and weight. We will validate the homogeneity of demographic characteristics and examine the variables between the two groups. The number of patients who change their medication dosage will also be counted, and the variations between the two groups and within each group will be analyzed. If measurement data follows a normal distribution and has homogeneity of variance, the data values will be reported as mean ± standard deviation (MD ± SD). Covariance analysis will be used to compare the data across different groups. If the data does not adhere to the assumed normal distribution, the median values (P25, P75) will be used to characterize it. The Mann-Whitney U nonparametric test will be used to compare between groups. The mean ± standard deviation will be used for the description of the continuous variables. Qualitative data will be expressed in terms of frequency and percentage. The student’s t-test will be utilized for comparing measurement data between two groups from baseline to the 6-month follow-up, while the rank sum test will be used for ranked data, and the χ2 test will be used for analyzing categorical data. A paired t-test was used for comparisons before and after treatment within a group, and an analysis of variance was used for comparisons among different groups. Repeated-measurement analysis of variance was used to compare groups at multiple observation points. A significance level of 2.5% will be used for all statistical analyses, using two-tailed testing. Subgroup analysis will be conducted to examine differences between different genders and across various age brackets.

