## Methods and analysis

### Hypothesis

We aim to provide definitive proof to validate the hypothesis that EA is not inferior to escitalopram (ESC) in the treatment of mild to moderate first-episode depression.

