### Sample size calculation

The non-inferiority hypothesis is based on the results of a previous study (11). HAMD-17, as the primary outcome, decreased by 11.3 points in the premedication group and by 10.2 points in the EA group, with an equal standard deviation of 11.5 points. Following these parameters, the proposed non-inferiority boundary is set at -4 points, with a level one type I statistical error equivalent to 0.025 and a desired statistical power standing at 80%. These calculations are supported by the analytical tools implemented in PASS 15.0. The results were obtained for a required sample size of 81 cases per group, and considering a 20% drop rate, 102 cases need to be included in each group, totaling 204 cases. The formula employed to determine the sample size in this trial was listed as:

$${\text{n}}_{\text{A}}={\text{k}}_{{\text{n}}_{\text{B}}}\;\text{and}\;{\text{n}}_{\text{B}}=\left(1+\frac{1}{\text{k}}\right){\left(\sigma \frac{Z_{1-\alpha }+Z_{1-\beta }}{\mu_{A}-\mu_{B}-\delta }\right)}^{2}$$

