## Discussion

An epidemiological study of people with depression over a 12-month period found that 26.6%, 53.4%, and 20.0% were classified as having mild, moderate, and severe depression, respectively (20). Failure to promptly relieve the depressive state and its accompanying symptoms during early episodes of depression can contribute to its aggravation or recurrence, leading to impaired functioning, reduced productivity, and an increased risk of suicide, which can ultimately result in significant public health and economic consequences (21, 22). The question we put forward in this clinical trial is whether EA is not inferior to ESC for treating mild to moderate first-episode depression. ESC has high efficacy and favorable acceptability in patients with depression in China (23–25). By utilizing an established and effective SSRI as a positive control, we can more precisely evaluate the potential benefits and risks of the novel treatment (EA) in comparison to the standard-of-care therapy (ESC). However, the delayed onset of antidepressant action can prolong patients’ depressive feelings. AEs may also hinder therapeutic effects and result in high dropout rates, which leads to a large proportion of depressed patients who struggle to achieve complete remission and experience relapse. Thus, it is imperative to explore alternative or complementary treatments for depression, particularly in the early phase of the disease (26).

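### Last observation carried forward is the only stated rule for missing week-12 HAMD-17 scores; it shrinks a true EA deficit that opens over time, and the set called ITT is not all randomised patients.

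*Protocol article*

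**What the plan says.** The Hypothesis section states that the trial is to show that "EA is not inferior to escitalopram (ESC) in the treatment of mild to moderate first-episode depression". Under Primary outcome, "The primary outcome will be the mean change in HAMD-17 score from baseline to week 12", and on the HAMD-17 schedule: "This outcome data will be collected at baseline, during the treatment phase (at 4, 8, and 12 weeks), and at the 16-, 24-, and 36-week" visits after treatment. A patient who leaves before week 12 can therefore have a last score from week 8, week 4 or baseline.

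The Statistical analysis section then makes three provisions:

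- Missing data: "any missing primary outcome data will be replaced by the last observed data point, in accordance with the ITT principle".
- The ITT population: qualified participants who meet the inclusion criteria, who "have received the intervention at least once, and have provided at least one outcome assessment".
- A second set: "a Per-Protocol Set (PPS) analysis will be employed to assess those participants who completed the trial without significant protocol violations".

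The sample size section sets 102 per group after "considering a 20% drop rate". No other rule for missing primary data is given, and nothing says that the two analysis sets must agree before non-inferiority is claimed.

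**The concern.** Carrying a score forward assumes that the patient would have stayed at that level until week 12. The planning figures in the sample size section are falls of 10.2 and 11.3 points, so an early score will usually understate the week-12 improvement.

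Two effects follow. First, if EA is truly worse and the gap widens with time, an early score carries only part of the gap, so the estimated deficit moves toward zero. In a superiority trial that costs power; in a non-inferiority trial it raises the chance of a false claim. Second, the arm that loses more patients, or loses them earlier, is penalised. That favours EA if it is the ESC arm and works against EA if it is the EA arm.

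The analysis set is a separate weakness. The ITT principle means analysing every randomised patient in the allocated arm. The set described drops those untreated, unassessed or ineligible, so it is a modified ITT set. The text also does not say whether a baseline score counts as an outcome assessment. If it does, a baseline value can be carried to week 12 as zero change.

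**Working it through.** **Inputs from the protocol article.** SD 11.5, margin 4 points, type I error 0.025 (taken as one-sided), 20% dropout, ESC week-12 improvement 11.3 (Sample size calculation); HAMD-17 at weeks 4, 8 and 12 (Primary outcome). The plan's number per group reproduces from its own 81: 81/0.80 = 101.25, rounded up to 102. Whether 81 itself follows from the stated means is a separate question, on which this point does not depend.

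**Assumed inputs.** The documents give no trajectory and no split or timing of dropout. ESC improvement is assumed to be 5, 8.5 and 11.3 points at weeks 4, 8 and 12. The EA deficit opens linearly to exactly the margin: 1.33, 2.67 and 4. EA improvement is then 3.67, 5.83 and 7.3. Dropouts are assumed to have the same means as those who stay.

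**Formula.** LOCF mean of an arm = p4 × (week-4 mean) + p8 × (week-8 mean) + (1 − p4 − p8) × (week-12 mean), where p4 and p8 are the shares last seen at weeks 4 and 8.

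*Equal dropout, 10% + 10% in each arm*
- ESC: 0.10 × 5 + 0.10 × 8.5 + 0.80 × 11.3 = 10.39
- EA: 0.10 × 3.67 + 0.10 × 5.83 + 0.80 × 7.3 = 6.79
- Estimated deficit 3.60; shift 0.40 toward EA

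*ESC 15% + 10%, EA 7.5% + 7.5%*
- ESC: 0.15 × 5 + 0.10 × 8.5 + 0.75 × 11.3 = 10.075
- EA: 0.075 × 3.67 + 0.075 × 5.83 + 0.85 × 7.3 = 6.918
- Estimated deficit 3.16; shift 0.84 toward EA

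*Reversed: ESC 7.5% + 7.5%, EA 15% + 10%*
- ESC: 0.075 × 5 + 0.075 × 8.5 + 0.85 × 11.3 = 10.618
- EA: 0.15 × 3.67 + 0.10 × 5.83 + 0.75 × 7.3 = 6.608
- Estimated deficit 4.01; shift about −0.01

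**False non-inferiority.** SE = 11.5 × √(2/102) = 1.610. Error = 1 − Φ(1.96 − shift/SE).

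| Dropout | Shift/SE | Error (nominal 2.5%) |
|---|---|---|
| 20% in both arms | 0.248 | 4.3% |
| ESC 25%, EA 15% | 0.523 | 7.5% |
| ESC 15%, EA 25% | −0.006 | 2.5% |

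**Cross-check under a different assumed course.** A simulation took half of the week-12 improvement as reached by week 4 and 80% by week 8, with SD 11.5. Its range is from half of the dropouts last seen at week 4 and half at week 8, to all last seen at week 4:
- 20% in both arms: 3.8% to 4.1%
- ESC 25%, EA 15%: 5.8% to 7.6%
- ESC 15%, EA 25%: 2.2% to 2.4%
- ESC 10%, EA 30%: 0.9% to 1.5%, so the bias is then clearly against EA

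**Baseline carried forward.** If every dropout's baseline were carried forward, the shift at the margin would be 0.20 × 11.3 − 0.20 × 7.3 = 0.80 with equal 20% dropout.

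The effect of leaving out randomised patients cannot be calculated, because the documents do not say how many there would be.

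**The case against.** **The dropout imbalance is assumed.** A reader might infer from the Discussion ("AEs may also hinder therapeutic effects and result in high dropout rates") that ESC patients will leave more often and that the rule therefore favours EA. The documents do not support that. The sentence is general background on antidepressants; the Adverse events section lists common events for EA as well; the article's own limitation on dropout cites follow-up length, which applies to both arms; and the 20% is applied equally. With the imbalance reversed, the inflation disappears. This objection stands. What remains without any imbalance is the shrinkage under equal dropout.

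**There is a per-protocol analysis.** It covers completers and needs no carried-forward scores. Under the illustration, where dropout is unrelated to outcome, a completer comparison is unbiased and its error stays near 2.5%, so it could expose the problem. This partly stands. If patients leave because of poor response or adverse events, conditioning on completion brings its own bias, and no rule says what follows if the two sets disagree.

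**The standard error.** A reader might add that single imputation understates the standard error. That does not hold here: each filled value is the patient's own earlier score, so patients stay independent. Simulating these scenarios with SD 11.5 at every visit gives a reported and an empirical standard error that both round to 1.62 with equal dropout. The fault is bias.

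**The nominal level.** The Statistical analysis section speaks of 2.5% two-tailed, which would be 1.25% in one direction. On that reading the first two errors become 2.3% and 4.3% against 1.25%. The figures change; the inflation does not.

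**Sensitivity analyses may sit in a plan not shown.** Their absence is not the fault raised here. The point is the primary rule that the article does fix. The repeated-measures analysis of variance it names is for comparing groups at several time points and is not offered as the way to handle missing primary data.

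**Conclusion.** The point holds in a conditional form. Carrying the last score forward is a poor primary rule for this non-inferiority question, and the set is mislabelled.

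At the documented SD, with a true deficit equal to the margin and equal 20% dropout before week 12, the rule hides about 0.4 of 4 points and raises false non-inferiority from 2.5% to about 4.3%. An ESC-heavy split raises it to about 7.5%; an EA-heavy split removes the inflation or turns the bias against EA. These sizes rest on assumed trajectories, timing and splits. They would be smaller if part of the 20% falls after week 12 or if patients mostly leave late. If the true difference is zero at every visit and dropout is the same in both arms, there is no shift.

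Severity: should be fixed. The documents do not support the stronger conclusion that the plan is biased toward EA.

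**What to change.** For the primary analysis:

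1. Include all randomised patients in their allocated arm.
2. Replace the carry-forward rule by a mixed model for repeated measures on the baseline and week 4, 8 and 12 HAMD-17 scores, or by multiple imputation. Treating baseline as one of the responses, or imputing, keeps patients who have only a baseline score.
3. Add a sensitivity analysis that worsens imputed EA scores in steps, and report how far they must worsen before non-inferiority is lost.
4. Keep last observation carried forward at most as a sensitivity analysis.
5. Call the present set a modified ITT or full analysis set, and say whether its outcome assessment must be after baseline.
6. State how the primary and per-protocol results will be read together if they differ.

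All the scores needed are already scheduled. The cost is analysis wording and modest programming, with no new visits or patients.

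### The non-inferiority decision is not tied to the -4 margin, and the per-protocol analysis has no stated part in it

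*Protocol article*

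**What the plan says.** The Hypothesis section of the protocol article sets out to "validate the hypothesis that EA is not inferior to escitalopram (ESC) in the treatment of mild to moderate first-episode depression". The endpoint is fixed under Primary outcome: "The primary outcome will be the mean change in HAMD-17 score from baseline to week 12". Under Sample size calculation, "the proposed non-inferiority boundary is set at -4 points", with a type I error of 0.025 entered in a one-sided formula, and "considering a 20% drop rate, 102 cases need to be included in each group".

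The Statistical analysis section defines the ITT population as eligible participants who were treated at least once and gave at least one outcome assessment, which is a modified ITT set. Missing primary data are filled with the last observed value. The per-protocol set (PPS) follows: "Additionally, a Per-Protocol Set (PPS) analysis will be employed to assess those participants who completed the trial without significant protocol violations". The tests listed are covariance analysis, t-test, Mann-Whitney, chi-square and analysis of variance, all at a two-tailed 2.5% level. The section contains neither the -4 margin nor a confidence-limit criterion, and it does not say how the ITT and PPS results are to be weighed. The abstract states that full details of the analysis plan for the primary outcome are in this article.

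**The concern.** In a superiority trial, patients who stop or do not adhere usually make the arms look alike, which works against the claim. In a non-inferiority trial the same dilution works in favour of it. The treatment schedule is 8 x 3 + 4 x 2 = 32 sessions plus daily tablets, yet one treatment and one assessment are enough to enter the ITT set. The protocol itself expects 20% to drop out.

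With no rule that ties the conclusion to -4, and none that links the two sets, the report could claim non-inferiority on the ITT result while the PPS, which is already planned, fails to support it. The one-sided 2.5% error rate behind the sample size would then not hold for the effect in patients who actually took the treatments.

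**Working it through.** **The plan's own figure.** The stated inputs are: "decreased by 11.3 points in the premedication group and by 10.2 points in the EA group", "with an equal standard deviation of 11.5 points", margin 4, one-sided alpha 0.025, power 80%. The formula is n = 2 x [11.5 x (1.960 + 0.842) / D]^2, where D is the distance from the assumed difference to the margin.

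- With EA 1.1 points worse, as stated, D = 4 - 1.1 = 2.9 and n = 247 per group.
- With EA and ESC equal, D = 4 and n = 130.
- With 1.1 added to the margin, D = 5.1 and n = 80 (81 using the t distribution).

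The stated 81 therefore appears only in the third case. The inflation 81 / 0.8 = 102 (rounded up) is correct. The direction of the 1.1 is a separate matter; here it affects only the cost of the fix.

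**Dilution scenario (assumptions).** Among adherent patients EA is truly 4 points worse, exactly at the margin. A share f of each arm contributes no treatment difference. All 102 per arm are analysed, with SD 11.5.

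- SE = 11.5 x sqrt(2/102) = 1.610.
- The ITT difference is -4 x (1 - f), so it lies 4f inside the margin. At f = 20% it is -3.2, which is 0.8 inside.
- P(non-inferiority declared) = 1 - Phi(z - 4f / SE).
- At f = 20%: 0.8 / 1.610 = 0.497. With z = 1.960, 1 - Phi(1.463) = 7.2%. With z = 2.241 (two-tailed 2.5%), 1 - Phi(1.745) = 4.1%.

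| f | ITT difference | One-sided 2.5% | One-sided 1.25% (two-tailed 2.5%) |
|---|---|---|---|
| 0 | -4.0 | 2.5% | 1.25% |
| 10% | -3.6 | 4.4% | 2.3% |
| 20% | -3.2 | 7.2% | 4.1% |
| 30% | -2.8 | 11.2% | 6.7% |

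**Simulation check.** 20,000 runs per setting, 102 per arm, a t-based 95% interval compared with -4, the non-adherent count rounded to whole patients (20 of 102 at f = 20%), and PPS membership unrelated to prognosis.

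| f | ITT alone | PPS alone | Both required |
|---|---|---|---|
| 10% | 4.0% | 2.4% | 2.1% |
| 20% | 6.9% | 2.6% | 2.2% |
| 30% | 10.8% | 2.4% | 2.1% |

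**Power at f = 20%, same simulation.**

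| True difference in adherent patients | ITT alone | Both required |
|---|---|---|
| EA 1.1 better | 86% | 78% |
| Equal | 70% | 57% |
| EA 1.1 worse | 48% | 33% |

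**The case against.** **The section is silent; it does not state a rule.** It plans both analyses and never says that ITT decides. A reader might infer from the additional status of the PPS that it has been made subordinate, but the text does not go that far. A separate analysis plan could supply the rule. This stands as a limit on the wording. It does not remove the gap, because the article says it gives the full plan for the primary outcome and then gives difference tests without the margin.

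**Whether the claim is false depends on the target.** If the question is the difference under whatever treatment patients actually take, a true -3.2 is inside the margin and declaring non-inferiority is correct. The 7% is an error rate only for the effect in adherent patients. The document does not say which it wants. This stands.

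**The scenario is a strong one.** Dropouts with a week 4 or week 8 score carried forward may keep part of the difference. If the required assessment must be post-baseline, the earliest dropouts leave the set altogether. Both would bring the rate down. A smaller SD would raise it (at SD 6, SE = 0.840 and the rate is 1 - Phi(1.960 - 0.952) = 16%), but the only SD in the document is 11.5, so the higher figures have no source there.

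**Carrying scores forward need not favour EA.** A reader might infer that it does, since the Discussion links adverse events to dropout and describes slow onset on antidepressants. The effect depends on which arm loses patients and when, and no dropout by arm is given. The direction is not established.

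**The PPS has its own bias.** It selects on events after randomisation, and the article does not define a significant violation. This is a reason to use it as a consistency check and not as a replacement for ITT.

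**Conclusion.** The point holds in a limited form. For a non-inferiority hypothesis the plan names two analysis sets but gives no margin-based decision rule and no rule for combining them, so non-inferiority could be claimed on the set more open to dilution.

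The size is about 7% against 2.5% (about 4% against 1.25% at the two-tailed level). It rests on four assumptions: the target is the effect in adherent patients, 20% of each arm contributes no difference, SD is 11.5, and 102 per arm are analysed. The true rate depends on adherence, which the document does not give.

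The documents do not support saying that the PPS has been ruled out of the decision, or that the false-claim rate will be as high as this. Nor do they show that a PPS of about 81 per arm is adequately powered because 81 was the calculated size. With EA 1.1 points worse, as stated, 81 per arm gives about 36% power: 2.9 / [11.5 x sqrt(2/81)] - 1.960 = -0.355. The PPS may also be smaller than 81 once protocol violators are removed.

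**What to change.** Add one rule to the Statistical analysis section: non-inferiority is concluded only if the lower limit of the 95% confidence interval for EA minus ESC improvement in HAMD-17 at week 12 lies above -4 in the ITT analysis of all randomised participants, and the PPS analysis supports the same conclusion. Fix PPS membership blind to arm before unblinding. Report disagreement between the two sets as inconclusive. The 95% interval matches the one-sided 0.025 of the sample size; the two-tailed 2.5% statement should be reconciled with it.

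Both analyses are already planned, so the rule needs no new data. The cost is power: in the scenario above, a loss of about 8 percentage points if EA is 1.1 better, 13 if equal and 15 if 1.1 worse. Because the PPS is open to selection bias, it serves as a consistency requirement alongside ITT and does not replace it.
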